### Outcomes {12}

The primary and secondary outcomes are based on the RE-AIM framework with effectiveness and implementation being the co-primary outcomes.

Primary and secondary effectiveness and implementation outcomes are fully described in Table 1. Exploratory secondary outcomes will include the extent to which participants are screened for other cardiovascular risk factors, counseled, and educated and documented in the EHR.

**Table 1 Tab1:** Effectiveness and implementation outcomes for InterCARE

Co-primary outcomes		
Effectiveness	Proportion of PLWH with diagnosed hypertension receiving anti-hypertensive medication with controlled blood pressure	EHR
Implementation	Proportion of clinic encounters in EHR where anti-hypertensive medications are prescribed if indicated	EHR
Secondary outcomes		Sources
Reach	· Proportion of eligible PLWH who agreed to be enrolled into InterCARE among those who met inclusion criteria · Proportion of PLWH who are aware of their hypertension status	· Modified EHR, DCF
Effectiveness	· Absolute difference in systolic and diastolic blood pressure between baseline, 12-month, and 24-month visits · The proportion of participants who scored > 70% on the heart disease fact questionnaire (HDFQ) · Proportion of PLWHIV with hypertension prescribed anti-hypertensive medications	· Modified EHR, DCF
Adoption	· Proportion of PLWH and HTN with 10-year CVD risk documented in EHR (E-CVDRF eval) · Proportion with BP documented in EHR · Proportion of those screened for other CVD risk factors using EHR · Proportion of those who received CVD risk factor counseling on anti-HTN medication, healthy diet, and appropriate physical activity levels · Proportion of PLWHIV with HTN enrolled in InterCARE receiving HTN and HIV care in the same clinic visit · Proportion of PLWHIV with HTN with BP control not on medication	· Modified EHR, DCF
Fidelity	· Proportion prescribed guideline concordant BP medication (as per Botswana 2016 Primary Care Guideline [17]) and/or major publication on management of BP among black Africans [18] · Proportion of treatment partners trained per protocol · Proportion of treatment partners providing support with the same frequency as expected · Proportion of intervention clinics that implemented the three components of InterCARE	· EHR, DCF, electronic trial logs
Feasibility	· Implementation of integrated HIV/hypertension care	· EHR, facility visit tracker, monitoring reports
Acceptability	· Acceptability of the implementation strategy · Patients, treatment partners, and provider’s attitudes towards InterCARE	· Surveys/key partners interviews
Maintenance	· Proportion of PLWH with HTN enrolled in InterCARE with BP control, who maintain BP control in next study visit	· EHR, DCF

*EHR* electronic health record, *DCF* data collection form, *PLWH*, people living with HIV, *E-CVDRF eval*, electronic-cardiovascular disease risk factor evaluation

See the participant timeline in Fig. 1.

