Key secondary outcomes	Reach (proportion of PLWHIV with hypertension who are aware of their hypertensive status) Adoption (proportion of PLWHIV with HTN prescribed anti-hypertensive medications in the EHR) Implementation fidelity (audit of intervention implementation as designed) Implementation feasibility (ability to implement integrated HIV/HTN care, HIV/HTN/CVD care etc.) Implementation acceptability (patient and provider survey and interviews) of the implementation strategy. Maintenance (provider and patient perceptions of ability to maintain plus change in blood pressure control from 12-24 months of the trial).

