### Sample size {14}

The InterCARE trial aims to recruit a total of 4652 PLWH with HTN across the intervention and control sites and up to 2326 treatments partners. Assuming unequal numbers of randomized controlled trial (RCT) enrollees per clinic, a within-clinic correlation of 0.055 [20], 10% refusal rate, 10% loss to follow-up at 12 months, a two-sided 95% confidence interval, and independent co-primary outcomes, we will need to enroll approximately 333 PLWH with hypertension on average per clinic from 14 clinics (Table 2). The number of participants to be enrolled per clinic assumes a 25% prevalence of hypertension [20] and will vary based on clinic volume. This sample size will provide > 90% power to detect achievement of intervention arm targets for all quantitative outcomes assessed within the RE-AIM framework. Of note, for all quantitative endpoint, we will have adequate power to detect smaller, yet still clinically relevant, intervention effect sizes.

**Table 2 Tab2:** Power calculations based on selected RE-AIM measures

	Proportion at study end				
Endpoint	Standard of care	Intervention targets	Absolute difference	Power to reach intervention targets	Minimum detectable difference with 90% power

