**Effectiveness**					
% PLWH w/diagnosed HTN receiving anti-HTN medication with controlled BP	19%	64%	45%	> 99%	21%

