## Data collection and management

### Plans for assessment and collection of outcomes {18a}

#### PLWH and HTN

Following informed consent, study data from participating PLWH will be collected at baseline and then at study visits at months 6, 12, 18, and 24 for the PLWH and their treatment partners. Socio-demographics, co-morbidities, medication intake, cardiovascular health data including a blood pressure assessment, and treatment partner sessions will be collected in the study electronic database.

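### The article gives two different Maintenance outcomes, and the Table 1 version, limited to participants already controlled after randomisation, is not a randomised comparison between arms

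*Protocol article*

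**What the plan says.** The protocol article states Maintenance twice.

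- **World Health Organization Trial Registration Data Set {2b}, key secondary outcomes:** provider and patient perceptions of ability to maintain, "plus change in blood pressure control from 12-24 months of the trial". Nothing restricts this to participants who were already controlled.
- **Outcomes {12}, Table 1, Maintenance row:** "Proportion of PLWH with HTN enrolled in InterCARE with BP control, who maintain BP control in next study visit". The Outcomes section refers the reader to Table 1 for the complete description of the outcomes, so Table 1 reads as the governing text.

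Participant data are "collected at baseline and then at study visits at months 6, 12, 18, and 24", so the next study visit is 6 months later. Statistical methods {20a} sends secondary binary outcomes to the same kind of generalized linear mixed model (GLMM) as the primary outcome, with treatment as fixed effect and cluster and pair as random effects. Table 1 also lists, under Effectiveness, "Absolute difference in systolic and diastolic blood pressure between baseline, 12-month, and 24-month visits".

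**The concern.** The two definitions answer different questions. The registration version asks whether the share of participants under control changes between months 12 and 24. The Table 1 version asks how often a participant who is controlled at one visit is still controlled 6 months later. With both in print, it is open which one will be reported as Maintenance. Blinding {17a} says the analysts are unblinded and follow interim site data, so the choice should be fixed in writing.

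The Table 1 version has a further problem. Its denominator is formed after randomisation by the response that the intervention is meant to alter. The two arms then contribute different kinds of patients, and randomisation no longer makes them comparable. BP varies from visit to visit. Where most of an arm lies above the cut-off, more of its controlled readings are chance lows that revert. Patients who become controlled only because of the intervention may also hold control more or less well than those controlled under usual care. A between-arm ratio mixes these effects with durability. It can stay favourable while the between-arm difference in control is shrinking.

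**Working it through.** **1. The two definitions side by side**

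| | Registration data set | Table 1 |
|---|---|---|
| Population | no restriction to controlled participants | only those controlled at a visit |
| Interval | months 12 to 24 | to the next visit, 6 months |
| Perceptions included | yes | no |

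**2. The plan's own figure.** Maintenance has no stated power. For the related Table 2 row, "PLWH w/diagnosed HTN receiving anti-HTN medication with controlled BP", the article gives 19% against 64%, power above 99% and a minimum detectable difference of 21%. The check used a pair-matched formula with 7 pairs, "a within-clinic correlation of 0.055", m = 332 per clinic and two-sided 5%:

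z(power) = sqrt[(7 − 2) × 0.45² / V] − 1.96, where V = (0.19 × 0.81 + 0.64 × 0.36) × (1 + 331 × 0.055) / 332 = 0.0222.

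This gives z of about 4.8, so power is above 99.9%. The minimum detectable difference at 90% power is 22%. The stated figures reproduce closely.

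**3. How the Table 1 measure behaves.** Inputs:

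- From Table 2: 19% (control) and 64% (intervention). These are study-end values that also require receipt of medication. Here they stand in for BP control at the earlier visit.
- Assumed, because the article gives no figure: BP at two visits is bivariate normal with correlation ρ.

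Formula: Maintenance = P(controlled at both visits) / P(controlled at the first visit).

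Worked case at ρ = 0.5:

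- Control, 19% at both visits: joint probability 0.0810, so 0.0810 / 0.19 = 43%.
- Intervention, 64% at both visits: 0.4847 / 0.64 = 76%.
- Intervention fading from 64% to 50%: 0.3976 / 0.64 = 62%.

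| ρ | Control, 19% steady | Intervention, 64% steady | Intervention, 64% to 50% |
|---|---|---|---|
| 0.3 | 32% | 71% | 57% |
| 0.5 | 43% | 76% | 62% |
| 0.7 | 56% | 82% | 68% |
| 0.9 | 75% | 90% | 75% |
| 0.95 | 82% | 93% | 77% |

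In the fading case the true between-arm difference drops from 64 − 19 = 45 points to 50 − 19 = 31 points. The Table 1 measure still favours the intervention at ρ of 0.3, 0.5 and 0.7. It is level at 0.9 and reversed at 0.95. With control steady at 19%, the intervention looks better until its own control falls below about 27% (ρ = 0.3), 32% (0.5), 39% (0.7) or 50% (0.9).

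**4. Counter-models, to test the direction**

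- Equal retention: if 70% of controlled participants keep control in both arms, the measure shows no difference, whatever share is controlled.
- Mixture: suppose the 19% who would be controlled under usual care keep control 80% of the time, and the extra 45% in the intervention arm keep it 60% of the time. The intervention arm then reads (0.19 × 0.80 + 0.45 × 0.60) / 0.64 = 0.422 / 0.64 = 66%, against 80% in control.

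So the sign depends on the correlation and on who becomes controlled.

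**The case against.** The strongest reply has five parts.

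- **The article does not rely on Table 1 alone.** The registration data set already lists the 12-to-24-month change, and the systolic and diastolic differences at 12 and 24 months could also show fading. This stands, so it would be wrong to say that Maintenance is defined only among controlled participants. It does not remove the conflict: both definitions are printed, and the BP differences are filed under Effectiveness.
- **The measure does respond to fading.** At ρ = 0.5 it falls from 76% to 62%. This stands. A reader might infer that the outcome cannot detect loss of effect, or merely repeats the effectiveness result. The document supports neither. What remains is that the between-arm ranking can stay favourable while the effect shrinks.
- **The bias has no fixed direction.** A reader might infer that the outcome automatically favours the arm with more control. The faded case at ρ of 0.9 and 0.95 and the two counter-models show otherwise.
- **The inputs are stand-ins.** The Table 2 percentages combine medication and BP and refer to study end, and the correlation is assumed. This stands, and the figures are an illustration only.
- **Maintenance is secondary.** It is absent from Table 2. The Abstract speaks of scale-up if the model succeeds, without naming Maintenance as the basis, so a claim that scale-up will rest on this outcome has no support.

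The article also does not say in so many words that Maintenance will be compared between arms. That follows from its general rule for secondary binary outcomes, and no exception is made for this one.

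**Conclusion.** The point holds in this form. The article contains two Maintenance outcomes that differ in population and interval and need to be reconciled. The Table 1 version conditions on a post-randomisation response, so a between-arm risk ratio from the planned GLMM would not be a randomised comparison. It is confounded with the level of control, in a direction that cannot be known in advance, and it can mask a shrinking effect.

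The size is illustrative. With no change over time, level alone gives gaps from 71% against 32% (ρ = 0.3) to 90% against 75% (ρ = 0.9). With a 14-point fade in the intervention arm, the gap runs from 57% against 32% to no difference over the same range. These figures rest on the assumed normal model, the assumed correlation and the Table 2 levels used as proxies. The definitional conflict and the loss of the randomised comparison depend on none of them. The change is worth making but not critical, because the co-primary outcomes and the sample size are untouched.

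**What to change.** Reconcile the two passages by making the registration measure the between-arm Maintenance outcome. Estimate BP control at months 12 and 24 in each arm among all enrolled participants, and compare the between-arm contrast at 24 months with that at 12 months. In the planned GLMM this means adding visit and arm-by-visit terms, with allowance for two readings per participant. Report the two differences in percentage points beside the risk ratios. The share of all enrolled participants who are controlled at both months 12 and 24 can support it. Keep the Table 1 conditional proportion, labelled as a within-arm description and not as a between-arm effect. Perceptions can stay as the qualitative part of Maintenance.

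No new data are needed, because months 12 and 24 are already study visits. The cost is a documented amendment to one secondary outcome. Recruitment is complete and the analysts are unblinded, so the change should be dated and, where possible, made before outcome data are compared by arm. Reporting the Table 1 proportion alongside keeps the change transparent.

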**Fig. 1 Fig1:**
[figure not shown]
Participant timeline {13} (SPIRIT Fig. [19]): InterCARE schedule of enrolment, interventions, and assessments

### Sample size {14}

The InterCARE trial aims to recruit a total of 4652 PLWH with HTN across the intervention and control sites and up to 2326 treatments partners. Assuming unequal numbers of randomized controlled trial (RCT) enrollees per clinic, a within-clinic correlation of 0.055 [20], 10% refusal rate, 10% loss to follow-up at 12 months, a two-sided 95% confidence interval, and independent co-primary outcomes, we will need to enroll approximately 333 PLWH with hypertension on average per clinic from 14 clinics (Table 2). The number of participants to be enrolled per clinic assumes a 25% prevalence of hypertension [20] and will vary based on clinic volume. This sample size will provide > 90% power to detect achievement of intervention arm targets for all quantitative outcomes assessed within the RE-AIM framework. Of note, for all quantitative endpoint, we will have adequate power to detect smaller, yet still clinically relevant, intervention effect sizes.

**Table 2 Tab2:** Power calculations based on selected RE-AIM measures

	Proportion at study end				
Endpoint	Standard of care	Intervention targets	Absolute difference	Power to reach intervention targets	Minimum detectable difference with 90% power
**Reach**					
% PLWH w/HTN aware of HTN diagnosis	46%	80%	34%	> 99%	23%
% PLWH w/diagnosed HTN receiving anti-HTN medication	42%	80%	38%	> 99%	23%

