### Eligibility criteria {10}

Patients are eligible if they (1) are aged between 20 and 75 years old, (2) have documented HIV infection and are on ART, (3) have a confirmed diagnosis of HTN or elevated systolic blood pressure (SBP) ≥ 140 or diastolic blood pression (DBP) ≥ 90 mmHg (or SBP ≥ 130 or DBP 80 mmHg if they have diabetes mellitus or chronic kidney disease), and (4) are a registered client at the selected clinics. PLWH are not eligible if they are documented as having a diagnosis of dementia in clinic records or if they are unable or unwilling to provide informed consent. PLWH and HTN will be selected for enrolment using a purposive random sampling method by trained research assistants at each site.

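### Table 2 powers hypertension awareness at study end on a 46% control rate that is not credible for a consented cohort selected for hypertension or raised blood pressure, so the >99% power claim for this Reach outcome is not supported

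*Protocol article*

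**What the plan says.** Table 1 of the protocol article (Outcomes {12}) lists as a secondary Reach outcome "Proportion of PLWH who are aware of their hypertension status", with the modified EHR and the data collection form as sources. It gives no time point. The registration data set also names awareness as a key secondary outcome.

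Table 2 (Sample size {14}) carries the row "PLWH w/HTN aware of HTN diagnosis" under the column heading "Proportion at study end": standard of care 46%, target 80%, difference 34 points, power above 99%, minimum detectable difference 23 points at 90% power. The sample behind the table is "approximately 333 PLWH with hypertension on average per clinic from 14 clinics", with "a within-clinic correlation of 0.055". The text claims more than 90% "power to detect achievement of intervention arm targets for all quantitative outcomes assessed within the RE-AIM framework".

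Under Eligibility criteria {10}, a patient in either arm must "have a confirmed diagnosis of HTN or elevated systolic blood pressure (SBP" or diastolic pressure) at or above a threshold. Research assistants take individual written consent ({26a}). Under {18a}: "Following informed consent, study data from participating PLWH will be collected at baseline and then at study visits at months 6, 12, 18, and 24", and these data include a blood pressure assessment. Section {20a} analyses secondary binary outcomes in the same way as the primary, with treatment arm as a fixed effect.

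**The concern.** A standard-of-care rate of 46% looks like a figure for people with HIV and hypertension in ordinary care. Table 2 uses it for control participants at the end of a trial they could join only with diagnosed hypertension or a raised reading, for which they signed consent, and in which the study assessed their blood pressure repeatedly. These steps apply equally in intervention and control clinics. They can raise awareness in the control arm without any contribution from the InterCARE package, and so narrow the difference the trial is meant to detect.

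Two things are at stake. One is a power claim that rests on an unsuitable control value. The other is interpretation: a small or null difference at study end could be taken as the package failing on reach, when enrolment itself had lifted both arms.

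**Working it through.** **Inputs from the documents.** Control 46% and target 80% at study end (Table 2); 14 clinics in 7 pairs; within-clinic correlation 0.055; about 333 enrolled per clinic; 10% loss to follow-up; two-sided 95% level; a formula for pair-matched cluster trials (note under Table 2). The exact formula is not printed.

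**Formula used.** With c = 7 pairs, m participants per clinic and ρ = 0.055:

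- V = [p0(1−p0) + p1(1−p1)] × [1/m + ρ(1−1/m)]
- power = Φ( (p1−p0) × √((c−2)/V) − 1.96 )

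For m = 300 (333 less 10%), the bracket is 0.00333 + 0.05482 = 0.05815.

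**Step 1: reproduce the plan.** 46% versus 80%: p0(1−p0) + p1(1−p1) = 0.2484 + 0.1600 = 0.4084, so V = 0.4084 × 0.05815 = 0.02375. Then 0.34 × √(5/0.02375) = 4.93, and Φ(4.93 − 1.96) = 99.9%. The result is practically the same for m = 333 and m = 270. The minimum detectable difference from 46% comes to 23.6 to 23.8 points, against 23 stated. The formula also comes close on two other rows: about 92% for 57% versus 80% (93% stated) and about 98% for 2% versus 20% (98% stated). The arithmetic in Table 2 is sound.

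**Step 2: what 46% requires.** At study end, 100 − 46 = 54% of control participants would have to be unaware of a hypertension diagnosis after selection, consent and up to five study visits (baseline and months 6, 12, 18 and 24). The article neither gives a source for the 46% nor argues that it fits this group.

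**Step 3: vary the control rate.** The documents give no figure for awareness among consented controls, so the values below are assumptions (m = 300, same formula).

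| Control | Intervention | Difference (points) | Power |
|---|---|---|---|
| 46% | 80% | 34 | 99.9% |
| 60% | 80% | 20 | 83.5% |
| 70% | 80% | 10 | 33% |
| 80% | 95% | 15 | 86% |
| 90% | 95% | 5 | 24% |
| 90% | 98% | 8 | 61% |
| 95% | 98% | 3 | 19% |
| 80% | 100% | 20 | 99.6% |
| 90% | 100% | 10 | 87% |

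The normal approximation is rough when one arm is at 100%.

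**Step 4: read the table.** With the 80% target kept, power is already below 90% at a control rate of 60%. Above 80% control awareness, the target lies below the control arm and the row no longer describes an improvement. Where control awareness is high, power depends on how far the intervention arm exceeds its target.

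**The case against.** **Nothing says that enrolment informs everyone.** A reader might infer that all participants in both arms learn their status at enrolment, so that no contrast can be observed. The documents do not support this. They state who takes consent, not what participants are told about their blood pressure. Patients may enter on a raised reading alone, control care is as usual, and the Table 2 endpoint is awareness of a diagnosis. Some control participants may never be given one and may report none. This part of the objection stands: compression is probable, but its extent is unknown and a ceiling in both arms is not shown.

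**The 23-point figure is not a fixed bar.** A reader might set a largest possible difference of 20 points, at 80% control awareness, against the stated minimum detectable difference of 23 points and conclude that the trial could not detect it. That is wrong. The 23 points belong to a 46% control rate, and binomial variance shrinks near 100%: 80% versus 100% still has about 99.6% power.

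**The denominator may be the whole clinic.** Table 1 does not restrict this outcome to participants enrolled in InterCARE, a phrase it does use for other outcomes. The wording therefore leaves a clinic-wide measure open, but the rest of the article does not fit it. The sources are the modified EHR and a study form, control clinics have no EHR modifications ({6b}), no sample of non-enrolled patients is described, and Table 2 is powered on enrollees.

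**It is only a secondary outcome.** True. Neither co-primary outcome uses awareness, and the row does not drive the sample size.

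**Conclusion.** The point holds in limited form. The 46% control rate is not a credible study-end value for a cohort assembled and followed in this way, and the >99% power rests on a contrast that the design itself erodes. Table 2 computes correctly from its inputs; the fault is in the choice of input.

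The size depends on two unknowns: control awareness among consented participants, and how far the intervention arm exceeds 80%. Over the assumed values, power runs from about 19% (95% versus 98%) to about 99.6% (80% versus 100%). The statement that every quantitative RE-AIM outcome has more than 90% power is therefore not established for this one. It does not follow that the trial cannot study awareness, or that the comparison is certain to be null. The results assume the pair-matched formula above, the stated correlation of 0.055 and 300 analysed participants per clinic.

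**What to change.** 1. Withdraw the 46% versus 80% awareness row from Table 2, or restate it with a control rate that can be defended for consented participants at study end, giving its source.
2. Exempt this outcome from the sentence claiming more than 90% power for all quantitative RE-AIM outcomes.
3. Keep awareness as a secondary outcome. It is in the registration data set and recruitment closed on 11 September 2023, so dropping it now would be a post-recruitment change of outcome.
4. Report baseline awareness by arm where the baseline data hold it. The article does not say whether the answer was taken before or after participants learned their reading, so the report should.
5. State in the analysis and reporting text that enrolment and study visits affect the end-of-study comparison in both arms, so that a null result is not read as failed reach.
6. Leave the enrolment-based Reach measure in Table 1 as it is.

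Switching to records of non-enrolled patients is not recommended. The article describes no such data source, and those patients would have no InterCARE treatment partner, so the measure would test a different exposure.

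The cost is wording, plus the loss of a power claim for one secondary outcome. No new data are needed, and the co-primary outcomes and the total of 4652 are unaffected.
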